#### ***Self-efficacy (transplant confidence)***

We measure participants’ self-efficacy (transplant confidence), which reflects their confidence that they can enact and sustain a behavior change [45] (in this case, the behavior change is receipt of a transplant or LDKT). We assess study participants’ confidence in their ability to pursue transplant and LDKT in difficult situations. For transplant in general, we ask “How confident are you that you could get a transplant even if…” for eight items and scenarios, such as “…your friends and family were unsupportive of you getting a transplant”. Similarly, six self-efficacy questions focus upon LDKT and ask “How confident are you that you could get a living donor transplant even if…”, followed by items and scenarios such as “…you don’t know anyone who might be a living donor for you”. Responses are on a 5-point Likert scale from “Not at all confident” to “Completely confident”.

#### ***Decisional balance (Pros and Cons of DDKT and LDKT)***

Decisional balance measures how patients are weighing the advantages and disadvantages (pros and cons) of transplant. We ask patients to rate the importance of possible positive and negative items related to patients’ decisions about DDKT and LDKT. We include 12 items regarding transplant in general and 12 items regarding LDKT. For each item, we ask, “How important is this statement to your decision about transplant/living donor transplant?” Sample statements include “I would live a longer life with a transplant” (Pro of transplant) and “I will feel guilty having someone donate to me” (Con of LDKT). Responses are rated on a 5-point Likert scale from “Not important” to “Extremely important”.

### Other collected variables

#### ***Prior actions taken to learn about transplant***

On the day of the transplant evaluation, we ask study participants about prior actions they had taken to learn about kidney transplant. These prior actions include: reading brochures about kidney transplant, reading brochures about LDKT, browsing Internet websites about kidney transplant, watching television or videos about kidney transplant, attending kidney disease support groups, talking to recipients of a kidney transplant, talking to doctors and medical staff about transplant, and talking to family and friends about transplant.

#### ***Health literacy***

On the day of the transplant evaluation, we assess study participants’ health literacy in two ways. First, we administer the Newest Vital Sign (NVS), a validated in-person measure of health literacy and numeracy [46]. The NVS assesses functional health literacy and numeracy and is scored from zero to six, with higher scores reflecting better health literacy. Scores of zero to three suggest limited health literacy [46].

Second, we use screening questions to inquire about the participants’ ability to read, comprehend, and fill out hospital forms [47,48]. These screening questions ask the study participant (1) “How often do you have problems learning about your medical condition because of difficulty understanding written information?” (always, often, sometimes, occasionally, or never); (2) “How often do you have someone help you read hospital materials?” (always, often, sometimes, occasionally, or never); and (3) “How confident are you filling out medical forms by yourself?” (extremely, quite a bit, somewhat, a little bit, or not at all). These questions are effective in identifying persons with limited health literacy [49].

### Final follow-up

After the 1-week and 3-month telephone interviews, study participants are followed for 12 months after their transplant evaluation. At that point, based upon our medical records, we determine whether the potential transplant candidate is placed on the waiting list at our center (and if not placed on the list, then the reason why) and whether the study participant is alive or not.

### Reimbursements and incentives for study participants

At the transplant evaluation, study participants receive a $15 gift card to a local supermarket, gas station, or retailer, as an incentive for study participation in either usual or intensive education. After the completion of the 3-month phone interview, a $10 gift card is mailed to the study participants. No additional incentives were given for completion of the 1-week or 3-month phone interviews.

### Statistical analysis

The initial data analysis will be descriptive. Participants’ baseline variables (demographics, medical characteristics, providers, etc.) will be described, using frequencies for categorical variables (such as race), and mean, median, range, standard deviation, and standard error of the means for continuous variables (such as age). Scatter plots of continuous variables and plots of means versus levels of categorical variables will be examined to assess bivariate relationships.

To determine whether randomization resulted in the desired equal distributions in the arms of the study, we will initially compare frequencies, means, and medians for baseline variables across the two study arms (usual vs. intensive education). Because the data are clustered by evaluation session, all significance tests (bivariate and multivariable statistical tests) will use generalized estimating equations (GEE), which account for variance determined by the cluster or “design effect” [50,51]. The analysis will use a per-protocol analysis. As a sensitivity analysis, we will perform an intent-to-treat analysis [52], in which we use multiple imputation for data that are missing. Multiple imputation allows intent-to-treat analysis by permitting inclusion in the analysis of all enrolled study participants [53].

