## Methods/design

### Study design summary

The ELITE study is a single-center, cluster randomized [36,37], parallel group clinical trial designed to test the effectiveness of an educational intervention [38] upon transplant candidates’ knowledge of LDKT (see Figure 1 for flow diagram and Additional file 1 for CONSORT 2010 checklist of information to include when reporting a cluster randomised trial). All study procedures were approved by the Institutional Review Boards at both Saint Barnabas Medical Center (SBMC, protocol number 2009–53) and the University of Medicine and Dentistry of New Jersey (protocol number 0120100096).

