### Intensive transplant education (experimental, Arm 2)

Potential transplant candidates who are cluster-randomized to intensive initial education (Arm 2) undergo the same education and evaluations as candidates in the usual education group. Additionally, study participants in the intensive education arm also undergo an intervention designed to increase knowledge of LDKT. This intervention is directed by the research nurse or assistant, who functions as a Transplant Educator. The intervention is based upon materials from the *Explore Transplant* series of kidney transplant education materials. When implemented in dialysis units, *Explore Transplant* has been shown to increase dialysis patients’ pursuit of DDKT and LDKT [40]. However, *Explore Transplant* has yet to be tested at a transplant center.

Our educational intervention consists of two parts, both implemented on the day of the transplant evaluation. First, study participants (together with any friends and family who accompanied them) view a 25-minute video, entitled “The experiences of living kidney donors”, from the *Explore Transplant* series of kidney transplant education materials [41,42]. This video, intended for potential transplant candidates, discusses how living donors came to their decision to donate; donors’ motivations and what they learned; facts about the donor evaluation, surgery, and recovery; risks to the living donors; and life after donation. The learning objectives of the video are to enable the viewer to understand the evaluation, surgery, and recovery process of living donors; learn possible risks that living donors face and how often these risks occur; learn the advantage of living donor kidneys versus deceased donor kidneys; and learn ways family member and friends can provide support to transplant candidates. The video features the stories of actual living kidney donors and presents accurate medical facts about LDKT, presented by medical professionals.

Second, after viewing the video, the study participants meet privately with the trained Transplant Educator for a fifteen-minute meeting to:

• Answer any questions that patients may have had, based upon what they saw in the video;

• Explore with patients their reasons for wanting a kidney transplant;

• Explore with patients their current situation with CKD/ESRD;

• Examine how the patients’ CKD/ESRD affects their family and friends;

• Answer any questions or concerns about transplant that the patient has;

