#### ***Primary analysis***

To evaluate the effects of the intensive versus usual transplant education, upon LDKT knowledge one week after the transplant evaluation, we will compare overall knowledge scores between groups of candidates. These knowledge scores will be calculated by totaling the number of correct responses (range 0–20). We will compare knowledge scores between the usual vs. intensive education groups using the two-sample t-test with GEE. Randomization assignment (usual vs. intensive education) will be the independent variable. To adjust for any baseline characteristics that are unequally distributed between the two study arms, and to examine and control for the effects of confounders and other covariates, we will use multivariable linear regression models with GEE to determine differences in knowledge between the two study arms (usual vs. intensive education).

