### Power and sample size calculations

Our primary analysis will determine whether the study intervention is associated with increased knowledge of LDKT, one week after the transplant evaluation. Because the randomization of patients is clustered by evaluation date, sample size and power calculations for testing the effect of the intervention must be based on the number of evaluation days randomized to each condition, the number of patients per evaluation day, the expected intra-class correlation (ICC) among patients within a cluster (ICC indicates within-group similarity on the outcome), and the estimated difference between conditions in, and variability of, transplant knowledge scores. Based on previous research [40], we estimate that patients in the intervention arm will have 10-20% higher transplant knowledge at 1 week post-baseline than patients in the standard-of-care arm. Assuming a conservative ICC of 0.4, we calculated that with 250 patients in each of the two study arms from approximately 100 evaluation days per study arm (2–3 patients per evaluation day), a two-sample t-test with type 1 error of 0.05 would have at least 95% power to detect a 10-20% difference in knowledge scores. In summary, to have sufficient power to detect differences in the primary and secondary outcomes, this study should include 250 patients in each education condition at 1 week post-evaluation.

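### Per-protocol is the main analysis of a superiority trial and intent-to-treat only a sensitivity analysis, so the headline result rests on a set selected after randomisation

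*Protocol article*

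**What the plan says.** The ranking is explicit in the article's Statistical analysis section: "The analysis will use a per-protocol analysis. As a sensitivity analysis, we will perform an intent-to-treat analysis". The one contrast it draws between the two concerns missing data: "Multiple imputation allows intent-to-treat analysis by permitting inclusion in the analysis of all enrolled study participants".

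The question is one of superiority and effectiveness. Study design summary describes a trial "designed to test the effectiveness of an educational intervention", and Power and sample size calculations says: "Our primary analysis will determine whether the study intervention is associated with increased knowledge of LDKT, one week after the transplant evaluation".

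The arms are nested. Intensive-arm participants "undergo the same education and evaluations as candidates in the usual education group", and in addition watch a 25-minute video and have a 15-minute meeting with a Transplant Educator, at no fixed point in the evaluation day.

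Under Primary analysis, "Randomization assignment (usual vs. intensive education) will be the independent variable". Participants are therefore compared by allocated arm and are not regrouped by what they received.

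Under Measurement timepoints, the article explains that knowledge, readiness, self-efficacy and decisional balance cannot be measured before education starts.

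**The concern.** When the question is whether one programme works better than another, the natural main analysis keeps every enrolled participant in the allocated arm. A per-protocol analysis conditions on something that happens after allocation, and whatever drives that event can differ between the arms.

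This trial has two features that sharpen the problem. First, the intensive arm is the usual arm plus two components. Someone in the usual arm who would have skipped the video cannot be identified, so a rule based on those components can remove people from one side only. Second, there is no baseline knowledge score. The planned regression can adjust for demographics, health literacy and prior transplant education, but not for what participants already knew. Allocation by evaluation date is therefore the main protection of the 1-week comparison, and a per-protocol primary analysis weakens it.

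At stake is which estimate becomes the headline result. The Discussion looks ahead to adoption in transplant centres generally, where some patients will miss parts of the programme. The all-enrolled analysis is the one that speaks to that use.

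**Working it through.** **The plan's own figure.** Inputs from Power and sample size calculations: 250 patients per arm, ICC 0.4, 2-3 patients per evaluation day (taken as 2.5), type I error 0.05 (two-sided assumed) and at least 95% power.

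- Design effect = 1 + (2.5 − 1) × 0.4 = 1.6.
- Effective n per arm = 250 / 1.6 = 156.25.
- Standardised difference detectable with 95% power = (1.960 + 1.645) × √(2/156.25) = 0.408 SD. It is 0.381 SD at 2 patients per day and 0.433 SD at 3.

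The article gives no SD and no control mean, so the stated power can be neither confirmed nor refuted. If 10% means 2 of 20 points, 95% power holds for an SD up to 2/0.408 = 4.9 points. If it means a relative gain of 1.2 points on an assumed control mean of 12, it holds up to 1.2/0.408 = 2.9 points. Nothing below depends on this; 0.408 SD serves only as a yardstick.

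**Shift from one-sided exclusion.** Let f be the share of the intensive arm excluded and d the number of SDs by which the excluded would score below the rest of the arm. Both are assumptions; the documents give neither. The full-arm mean equals the mean of the rest minus f × d, so excluding these people raises the arm mean by f × d:

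- f = 0.10, d = 0.5: 0.05 SD, or 0.05/0.408 = 12% of the detectable difference.
- f = 0.20, d = 0.5: 0.10 SD, or 0.10/0.408 = 25%.

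**Type I error with no true effect.** Standard error = √(1.6/[250(1 − f)] + 1.6/250), holding the design effect at 1.6. Rejection probability = Φ(f·d/SE − 1.96) + Φ(−f·d/SE − 1.96).

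For example, at f = 0.20 and d = 0.5: SE = √(1/125 + 1/156.25) = 0.120, the ratio is 0.833, and the probability is 0.130 + 0.003 = 0.133.

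| f | d | shift (SD) | two-sided type I error |
|---|---|---|---|
| 5% | 0.5 | 0.025 | 0.055 |
| 10% | 0.5 | 0.05 | 0.071 |
| 20% | 0.5 | 0.10 | 0.133 |
| 10% | 1.0 | 0.10 | 0.138 |
| 20% | 1.0 | 0.20 | 0.385 |
| any | 0 | 0 | 0.05 |

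**Cost of the alternative.** Suppose the true effect among those reached is 0.408 SD and a share of the intensive arm gets no benefit. The intent-to-treat effect is then 0.408 × (1 − share), and power falls from 95% to about 93%, 90% and 82% for shares of 5%, 10% and 20%.

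**The other reading.** If per-protocol means those with a completed 1-week interview, the calculation above does not apply. Loss can occur in both arms, and bias arises only if the reasons for loss, in relation to knowledge, differ between them. The documents give no figure from which to size this.

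**The case against.** The strongest reply is that the article defines no per-protocol set and gives no exclusion rate, and that a condensed article may leave the definition to the full protocol. Its only contrast between the two analyses is missing data, so the main analysis may be no more than an available-case analysis by randomised arm. Usual-arm participants can deviate too: they have a 90-minute presentation and a series of team meetings to attend. The added components are short, take place on the same day and are led by research staff, so non-completion could be well under 10%. Those who skip the video might already be well informed, which would reverse the bias. Finally, intent-to-treat is prespecified, so any divergence between the two analyses can be examined.

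Most of this stands, and it rules out a stronger reading. A reader might infer that exclusions fall almost wholly on the intensive arm, that the bias certainly favours it, and that the randomised comparison is lost. The documents support none of these. Only exclusions for missing the added components are confined to the intensive arm; the direction is plausible but not established; and the intent-to-treat analysis is still planned.

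The reply does not remove the problem of ranking. That ranking is stated outright, so it is not a detail left to another document. On either reading the main analysis omits enrolled participants because of something that happened after allocation. Keeping randomised arm as the independent variable prevents regrouping, not exclusion.

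**Conclusion.** The point holds as one about ranking. A superiority trial of effectiveness takes its headline result from a set selected after randomisation and treats the all-enrolled analysis as a check. Neither the size nor the direction of any bias can be read from the documents.

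If the set excludes people who missed the video or meeting, bias in favour of the intensive arm is plausible. With 10-20% excluded and a 0.5 SD deficit, both assumed, it amounts to 0.05-0.10 SD and a type I error of about 0.07-0.13. At 5% excluded it is close to negligible, and with no score difference it vanishes. If the set is interview completers, the selection can affect both arms and its effect is unknown.

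**What to change.** Make intent-to-treat the primary analysis: all enrolled participants, analysed by the arm of their evaluation date, whether or not they completed the video and meeting. Participants who missed a component but gave a 1-week interview enter with their observed score. For missing scores, use the multiple imputation already planned, with arm and the clustering by evaluation date reflected in the imputation model. Report per-protocol as the sensitivity analysis and state which participants it excludes. Apply the same order to the secondary outcomes.

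This takes a few sentences of analysis text. No new data are needed and both analyses are already planned. The price is a possibly diluted estimate, and power somewhat below the stated 95% if part of the intensive arm misses the intervention (about 90% if one in ten gets no benefit, at an effect that would otherwise give 95%). Imputation also carries its own assumption about why scores are missing, which should be stated.

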#### ***Primary analysis***

To evaluate the effects of the intensive versus usual transplant education, upon LDKT knowledge one week after the transplant evaluation, we will compare overall knowledge scores between groups of candidates. These knowledge scores will be calculated by totaling the number of correct responses (range 0–20). We will compare knowledge scores between the usual vs. intensive education groups using the two-sample t-test with GEE. Randomization assignment (usual vs. intensive education) will be the independent variable. To adjust for any baseline characteristics that are unequally distributed between the two study arms, and to examine and control for the effects of confounders and other covariates, we will use multivariable linear regression models with GEE to determine differences in knowledge between the two study arms (usual vs. intensive education).

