• Review a brochure from *Explore Transplant*, “Why Kidney Patients Get Transplants/Why People Donate Their Kidneys”;

• Review a fact sheet from *Explore Transplant*, “Possible Risks to Living Donors”; and

• Review a fact sheet from *Explore Transplant*, “Living Donors’ Evaluation, Surgery, and Recovery”.

Because the order in which potential transplant candidates meet with team members is unsystematic, the viewing of the video and meeting with the Transplant Educator occur at any point during the transplant evaluation.

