#### ***Secondary analyses***

As a secondary outcome, we will also assess change in transplant knowledge from 1 week post-evaluation to approximately three months after the transplant evaluation. In this analysis, the outcome will be measured as “difference scores” (the 1 week knowledge score subtracted from the three month knowledge scores) using linear regression with GEE and adjusting for unequally distributed baseline characteristics [54].

We will determine the impact of the study intervention upon the other secondary outcomes: (1) readiness to pursue transplant and LDKT at 1 week post-evaluation; (2) self-efficacy regarding transplant and LDKT at 1 week post-evaluation; (3) decisional balance regarding transplant and LDKT at 1 week post-evaluation; and (4) changes in readiness, self-efficacy, and decisional balance regarding transplant and LDKT, from 1 week to 3 months post-evaluation. Self-efficacy, decisional balance, and change in self-efficacy and decisional balance are measured on a continuous scale, so they will also be analyzed with linear regression with GEE. Readiness to pursue transplant and LDKT will be analyzed as dichotomous outcomes, where the probability of patients being in Action or Maintenance vs. the probability of being in Pre-contemplation, Contemplation, or Preparation will be modeled with logistic regression with GEE. The tests for all secondary outcomes will also be adjusted for any unbalanced baseline characteristics.

Finally, to examine how key barriers to LDKT work alone and in combination with our intervention to impact LDKT knowledge, we will test the independent effects of race, previous actions taken to learn about transplant, and health literacy on knowledge at 1 week post-baseline. We will also test whether these variables interact with the intervention to effect knowledge of LDKT. We will model knowledge of LDKT as the dependent variable using multivariable linear regression models with GEE. To fit the models, we will use forward selection procedures where independent variables that are univariately significant at P < 0.20 will be eligible for inclusion in the multivariable model. Those variables significant at P < 0.05 in the multivariable models will be retained [55].

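### The primary analysis does not say whether the unadjusted or the adjusted comparison decides the trial, and the adjusted model takes its covariates largely from observed arm imbalance

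*Protocol article*

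**What the plan says.** The Primary analysis section of the protocol article begins with an unadjusted comparison: "We will compare knowledge scores between the usual vs. intensive education groups using the two-sample t-test with GEE". Randomised arm is the only independent variable. The section then adds a second analysis of the same contrast: "we will use multivariable linear regression models with GEE to determine differences in knowledge between the two study arms".

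Two reasons are given for the second model. One is imbalance: "To adjust for any baseline characteristics that are unequally distributed between the two study arms". The other is open-ended: "to examine and control for the effects of confounders and other covariates". The section names no covariate, gives no threshold for imbalance, and does not rank the two analyses.

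The opening of Statistical analysis supplies the check that feeds the first reason. "To determine whether randomization resulted in the desired equal distributions in the arms of the study", it says, "we will initially compare frequencies, means, and medians for baseline variables across the two study arms". Secondary analyses extends the rule: "The tests for all secondary outcomes will also be adjusted for any unbalanced baseline characteristics".

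Power and sample size calculations rests on a two-sample t-test. Study aims names Black race, less prior transplant education and lower health literacy as known barriers to living donor transplant. All three are recorded on the evaluation day. Secondary analyses tests them as predictors of knowledge, but nothing fixes them as covariates for the primary comparison. The article explains that knowledge cannot be measured at baseline.

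**The concern.** Imbalance and prognostic value are different properties. Under sound randomisation, a difference between arms in a baseline variable is chance, and its size does not show whether the variable predicts the knowledge score. An imbalance rule can therefore bring in a weak predictor that happens to differ and give no reason to include a strong one that happens to balance. The open clause on confounders could admit the strong one, but it does so by a choice that the text leaves unmade.

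Two things are at stake. The adjusted estimate depends on the data, and with the two analyses unranked a reader cannot tell in advance which result is the trial's answer. Precision is also given up. With no baseline knowledge score, the patient characteristics already collected are the only route to it.

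A related point concerns prior actions to learn about transplant. Those items ask about brochures, videos and talks with medical staff, which overlap with the intervention. They are sound covariates only if they are asked before the intervention, and the article does not state that order.

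**Working it through.** **Inputs.** From Power and sample size calculations: 250 patients per arm, about 100 evaluation days per arm, 2–3 patients per day (2.5 used here), ICC 0.4, type I error 0.05 (two-sided assumed), power at least 95%. The SD and control mean are not given, so effects are in SD units. The share of score variance explained by covariates, R², is not given either; 0.1–0.3 is an assumption.

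**1. The plan's own design.** Design effect = 1 + (2.5 − 1) × 0.4 = 1.6. Effective n = 250 / 1.6 = 156 per arm. Detectable difference at 95% power = (1.96 + 1.645) × √(2/156.25) = 0.408 SD (0.381 with 2 patients per day, 0.433 with 3). If a 10% difference means 2 of 20 points, the stated power holds for an SD up to 2 / 0.408 = 4.9 points. The stated power is attainable but cannot be verified without the SD.

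**2. How often chance triggers adjustment.** With K independent baseline variables each checked at 0.05, P(at least one flagged) = 1 − 0.95^K. That is 23% for K = 5, 40% for K = 10 and 54% for K = 15.

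**3. What fixed adjustment gains.** Set the score variance to 1. Let the covariates explain R² and vary independently of visit day, and let the remaining 1 − R² have ICC 0.4. The variance of an arm mean is proportional to 1.6(1 − R²) + R² unadjusted and 1.6(1 − R²) adjusted, so the variance ratio is 1.6(1 − R²) / [1.6(1 − R²) + R²].

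| R² | Variance ratio | SE ratio | Worth in patients | 0.408 × SE ratio |
|---|---|---|---|---|
| 0.1 | 1.44/1.54 = 0.935 | 0.967 | +7% | 0.395 |
| 0.2 | 1.28/1.48 = 0.865 | 0.930 | +16% | 0.379 |
| 0.3 | 1.12/1.42 = 0.789 | 0.888 | +27% | 0.362 |

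The 0.408 starting value treats 0.4 as the ICC of the unadjusted score. On that reading throughout, the variance ratio is (1.6 − R²)/1.6, which is 0.9375 at R² = 0.1 and 0.8125 at R² = 0.3. The SE then falls by 3–10%, worth 7–23% more patients, and the detectable difference is 0.395–0.368 SD. The two readings barely differ.

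If the covariates clustered by day as strongly as the score, the variance ratio would be 1 − R². The SE would fall by 5–16%, worth 11–43% more patients.

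**4. What the imbalance rule recovers.** The simulation used 200 days of 2 or 3 patients, residual ICC 0.4, 10 independent covariates, a true effect of 0.32 SD, selection at baseline p < 0.05, cluster-robust linear models and 3,000 replicates.

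| R² | Power, unadjusted | Power, imbalance-selected | Power, pre-specified |
|---|---|---|---|
| 0.1 | 81.3% | 81.6% | 83.4% |
| 0.2 | 81.7% | 81.9% | 87.2% |
| 0.3 | 84.0% | 84.7% | 91.7% |

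At R² = 0.3 the mean SE was 0.107 unadjusted, 0.107 imbalance-selected and 0.095 pre-specified. The ratio 0.095/0.107 = 0.89 agrees with step 3.

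**5. Type I error.** Under the null (5 or 10 covariates, 4,000 replicates), the imbalance-selected model rejects in 4.2–5.1% of trials. Accepting either it or the unadjusted test gives 4.8–5.8%. Accepting either the unadjusted or a fully adjusted result gives 6.1–8.0%, although the fully adjusted model alone rejected in 4.8–6.0%, so not all of that excess comes from having a choice. The unadjusted and imbalance-selected tests disagree on significance in 0.7–1.8% of null trials and in 2–3% at 0.32 SD.

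**The case against.** The strongest reply is that the plan can be read sensibly as it stands. The t-test comes first, arm is its only independent variable, and the sample size is built on a t-test. The adjusted model then looks like a follow-up, and on that reading the primary estimate does not depend on the data. A reader might infer that the protocol formally declares two primary analyses. It does not: it puts both under one heading and leaves the ranking unsaid. What stands against the plan is the missing ranking.

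It is also fair that imbalance is not the only criterion. The clause on confounders and other covariates allows prognostic variables in, so the text does not support saying that the plan excludes strong predictors that balance. Yet the clause names nothing, and so widens the choice. A full analysis plan might supply a list. The imbalance trigger, however, is a stated rule and not an omitted detail, and a plan that followed it would carry it forward.

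Because days are randomised before patients consent, some imbalance could reflect who enrols and not chance alone. Covariates fixed for their prognostic value are still the better response.

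On the order of forms, a reader might infer that the questionnaires follow the video. The article does not show this. It says that "the viewing of the video and meeting with the Transplant Educator occur at any point during the transplant evaluation", and that the research meeting, with consent and initial questionnaires, may also fall anywhere in the day. It gives the video to study participants, which suggests that consent comes first. The order is unstated, not shown to be wrong.

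Finally, stated power is already at least 95%, so the lost precision is a matter of efficiency and does not make the comparison invalid. That is correct.

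**Conclusion.** The concern holds in a limited form. The deciding analysis is not named. The adjusted model's covariates come from observed imbalance plus an open clause, and the imbalance rule also governs the secondary outcomes. The adjusted estimate therefore depends on the data, and imbalance selection adds at most 0.7 percentage points of power over no adjustment in the simulation, against 2.1 to 7.7 points for covariates fixed in advance.

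The size is modest: a standard error about 3–11% lower, worth about 7–27% more patients, and a 95%-power detectable difference of about 0.36–0.40 SD instead of about 0.41 SD. This rests on an assumed R² of 0.1–0.3, covariates that do not cluster by visit day, ICC 0.4 and 2.5 patients per day. The article gives no figure for how well these variables predict knowledge, so the true gain could lie outside this range. The larger gain of 5–16% would need covariates that cluster by day as strongly as the score; nothing in the article suggests that health literacy or race does.

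A reader might also infer serious inflation of type I error. The calculations do not support that: choosing between the unadjusted and imbalance-selected results gives at most 5.8%. The change is worth making before the data are seen, but the trial's validity does not depend on it.

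**What to change.** Name one primary analysis: a linear GEE of the 1-week knowledge score on arm, NVS health literacy score and race, with the covariates fixed in advance and used whatever balance is observed. Add prior actions to learn about transplant only if that form is completed before the video and the educator meeting, and state that order in the protocol; otherwise leave the variable out of the model. Report the unadjusted comparison as supportive. Remove the imbalance trigger for the primary and all secondary outcomes, and keep the baseline comparison as description only.

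The cost is a few sentences of analysis text and, if prior actions are to be used, one line on the order of the day's forms. Every variable is already collected, and the sample size need not change.
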